#### Patient and public involvement

People with lived experience of MID and substance abuse were involved in the developmental phase of Beat the Kick. They contributed feedback on intervention materials (e.g., visual aids, examples) and pilot-tested sessions to ensure accessibility. They will also be involved in dissemination activities, including co-creating accessible summaries and video materials.

### Who will obtain informed consent? {26a}

Recruitment will be conducted jointly by researchers from Tilburg University and care professionals at the participating organizations: care professionals identify and pre-screen eligible clients and introduce the study; Tilburg University researchers then confirm eligibility, provide standardized information in accessible formats, and obtain written informed consent. Researchers from Tilburg University with expertise in intellectual disabilities and substance abuse will be responsible for obtaining informed consent. They will ensure that all participants, or their legal representatives where applicable, fully understand the nature of the study, the intervention, and any potential risks or benefits. This process will be guided by the Zelen design, which facilitates ethical and transparent participant engagement.

Participants randomized to the intervention group (Beat the Kick) will be approached after randomization. Researchers will provide a detailed explanation of the intervention and study procedures, seeking their consent to participate in both the intervention and the study assessments, such as questionnaires and interviews. Participants randomized to the CAU group will be informed of their allocation and asked to consent to participate in the study assessments only, which are essential for evaluating study outcomes but do not involve active participation in the intervention. The primary goal is to seek consent directly from participants whenever possible. In cases where a legal representative is required, formal consent will also be obtained from the representative, in compliance with Dutch law and ethical guidelines. Consent from both the participant and their representative will be required, as the participant’s engagement is crucial for a motivation-based intervention. Researchers will use tailored communication strategies, including clear language and visual aids, to address any questions or concerns and ensure participants’ comprehension of the study details.

All questionnaires will be completed digitally or on paper, with assistance from the researcher if needed, ensuring accessibility and efficiency in data collection. Model versions of the participant information sheet and consent form for both study groups are provided as supplementary materials (Additional files 1 and 2).

### Additional consent provisions for collection and use of participant data and biological specimens {26b}

There are no plans for the collection of biological specimens in this study. However, participants will be informed about the potential use of their data in future ancillary studies and will have the option to provide separate consent for this purpose. The consent forms will clearly outline data confidentiality, usage, and the right to withdraw consent for future data use at any time, without affecting their participation in the main study. This approach, approved by the Ethics Review Board of Tilburg University (RP 1983), ensures that participants or their legal representatives can make informed decisions regarding the use of their data. Additionally, any future research utilizing this data will require approval from an independent ethics committee to ensure adherence to ethical standards and the protection of participants’ rights and privacy.

## Intervention

### Explanation for the choice of comparators {6b}

The comparator in this study is the CAU condition. This choice enables a direct evaluation of the effectiveness of the Beat the Kick intervention relative to the standard care typically provided to people with MID and substance abuse problems. Participants in the CAU group will receive support from their intellectual disability healthcare organization, which may involve a multidisciplinary team including physicians, nurses, psychologists, social workers, and counselors.

Standard care in the CAU group encompasses a wide range of approaches tailored to individual needs. These may involve techniques to enhance readiness for change, as well as strategies focused on building supportive relationships between the individual and their caregiver. The aim is to create a stable and safe environment in which individuals feel valued and engaged in meaningful daily activities that foster a sense of competence and reduce challenging behaviors. Standard care may also include guidance, information, and assistance related to substance use and intellectual disabilities, along with regular check-ups to monitor progress, assess needs, and provide general support. Participants in the CAU group will not receive the structured Beat the Kick intervention. However, they will continue to receive care from their regular healthcare providers, including support related to substance use and intellectual disabilities. This ensures that all participants receive an ethically appropriate level of baseline care while allowing for a valid comparison with the added value of the intervention.

In addition, the use of a CAU comparator rather than a waitlist control helps prevent bias that could arise from nocebo effects. Participants placed on a waitlist may experience demoralization, reduced motivation, or worsening of symptoms due to the absence of support, which can artificially inflate the intervention’s observed effectiveness. By comparing Beat the Kick to the care that is actually available in practice, the study maintains both clinical relevance and methodological integrity.

### Intervention description {11a}

The Beat the Kick intervention consists of ten weekly individualized sessions, each lasting 45–60 min, designed to help participants understand and change their substance abuse patterns, identify triggers, and adopt healthier coping strategies. The intervention draws upon Self-Determination Theory [26] and Motivational Interviewing [33] to foster autonomous motivation. It does so by supporting the basic psychological needs of autonomy, competence, and relatedness, and by creating a safe, supportive environment in which participants are encouraged to explore and commit to meaningful behavior change.

Each participant is guided by a healthcare professional who has completed the “Train the Trainers: Beat the Kick” program. The program begins with an introductory session in which the trainer builds rapport, discusses expectations, and tailors the intervention to the participant’s specific needs and circumstances. To prevent potential carry-over effects, staff members supporting participants in the intervention group will not simultaneously support participants in the CAU group. This separation ensures that intervention-specific knowledge and techniques are not inadvertently applied in the control condition, preserving the integrity of the comparison.

Subsequent sessions are structured thematically. The second and third sessions help participants explore their substance use behaviors and attitudes through interactive activities such as online assignments, video clips, and discussions. Concepts like the distinction between substance addiction and substance abuse are clarified with visual aids. In sessions four through six, cognitive-behavioral techniques are introduced using the ABC model [34], which links triggers, beliefs, and behaviors. These sessions focus on identifying craving triggers and developing healthier responses.

Session seven emphasizes identifying personal values and interests to explore alternative activities that can replace substance use, while session eight focuses on evaluating the participant’s social network and identifying individuals who can offer support during challenging moments. The final two sessions consolidate the learnings by developing a personalized action plan and discussing options for ongoing support. The program concludes with a certificate recognizing participants’ efforts.

Before the intervention starts, participants’ regular support staff attend a 1.5-h clinical briefing session delivered by the trainer. This session is designed to improve staff members’ understanding of substance use and the intervention content, enhancing their ability to support participants appropriately. Additionally, a helper from the participant’s own social network provides ongoing support throughout the intervention period, offering a trusted and accessible source of encouragement and reflection.

### Criteria for discontinuing or modifying allocated interventions {11b}

Participants may discontinue the intervention for various reasons. They are free to withdraw from the study at any time without providing an explanation, and their autonomy in making this decision will be fully respected. If a participant’s condition deteriorates, for example due to increased substance use, the onset of severe psychiatric symptoms, or emerging safety concerns, healthcare professionals may advise discontinuation of the intervention in order to safeguard the participant’s well-being.

Discontinuation may also be considered if the participant experiences substantial emotional distress or other adverse effects that appear to be directly related to the intervention. In situations where participants consistently miss sessions or have difficulty engaging with the intervention, additional support will be offered to promote continued involvement. Whenever possible, modifications will be made in collaboration with the participant and their caregiver to enhance engagement, rather than opting for discontinuation. All forms of discontinuation, including partial disengagement such as repeated absences or reduced participation, will be documented and may be analyzed as outcomes in their own right. These instances may provide valuable insight into motivational dynamics or barriers to sustained participation.

If a participant voluntarily initiates formal addiction treatment during the study period, this will be recorded as a meaningful outcome rather than treated as a reason for discontinuation. This step will be interpreted as an indication of increased autonomous motivation to change, provided the decision to seek treatment is made voluntarily and not due to external pressure.

### Strategies to improve adherence to interventions {11c}

Several strategies will be employed to promote adherence to the intervention. A coordinated team, including trainers, supervisors (such as senior practitioners or clinical leads overseeing intervention fidelity), and the primary researcher as the independent monitor, will work together to ensure fidelity and quality. Trainers will be carefully selected from organizations familiar with the intervention’s goals and context. They will meet specific qualifications, including expertise in intellectual disabilities and addiction and, ideally, knowledge of MI. These trainers will receive formal training through RINO Zuid, a Dutch institute specializing in mental health and social care professional development, which includes theoretical instruction, practical exercises, and ongoing supervision to ensure high-quality and consistent delivery of the intervention.

Supervisors will provide regular oversight and feedback to trainers, addressing challenges to maintain fidelity. The independent monitor (primary researcher) will periodically review intervention sessions by analyzing session recordings or attending selected sessions, ensuring adherence to protocols and providing objective feedback to trainers. Trainers will also remain available for participant questions and concerns between sessions, but no additional structured check-ins will be required to maintain feasibility. The intervention will be tailored to align with each participant’s personal goals and needs, ensuring relevance and sustained motivation.

Fidelity will be monitored through detailed documentation, including trainer-completed checklists after each session, and regular reviews by the monitoring team to assess adherence to established protocols. Discrepancies or concerns will be addressed promptly through research team meetings, enabling continuous improvement in adherence strategies.

### Relevant concomitant care permitted or prohibited during the trial {11d}

Participants will continue receiving standard care from their healthcare organizations, which may include psychosocial support, medical check-ups, and general counseling. If participants voluntarily initiate other structured substance use treatment programs during the study period, this will be documented as a meaningful outcome rather than considered a reason for discontinuation. Such a step will be interpreted as an indicator of increased autonomous motivation to change, provided it is initiated voluntarily and not under external pressure. This approach ensures that the study can accurately assess the specific impact of the Beat the Kick intervention on motivational and substance use outcomes.

Participants will not be permitted to participate in other research trials related to substance abuse treatment during the study period. All concurrent treatments and support services will be thoroughly documented and considered in the analysis to evaluate their potential influence on study outcomes.

### Provisions for post-trial care {30}

After the intervention, participants interested in additional support will be provided with information about follow-up options through their healthcare organizations. Trainers will work with participants to identify suitable follow-up options tailored to their needs, such as individual counseling or, where available, more intensive substance abuse treatment. Given existing treatment gaps and regional differences in service accessibility, efforts will be made to align follow-up advice with realistic options within participants’ local care networks. Any participant experiencing distress related to the intervention will receive appropriate psychological support, including counseling or referrals to specialized services.

### Outcomes {12}

The primary outcome is the change in autonomous motivation for substance-abuse treatment, measured using an adapted version of the TSRQ [21]. The TSRQ comprises 15 items rated on a 5-point Likert scale (1 = completely untrue; 5 = completely true). Subscales are scored as means (range 1–5) and include autonomous motivation (internal consistency α≈0.84; primary endpoint), controlled motivation (α≈0.78), and amotivation (α≈0.41; analyzed exploratorily due to lower reliability). As participation in the intervention and any subsequent treatment is voluntary, baseline motivation may be relatively high; this will be considered when interpreting change. Assessments will occur at pre-treatment (T1), post-treatment (T2), and follow-ups at 1 month (T3) and 6 months (T4), with the primary endpoint defined as Δ(T2–T1) on autonomous motivation and maintenance examined at T3/T4. To optimize comprehension for MID/BIF participants, all self-reports will be interviewer-assisted.

Secondary outcomes include reductions in substance use and related problems, measured with the SumID-Q (patterns, frequency, consequences), which embeds the AUDIT and DUDIT screens. The AUDIT has 10 items (item scores 0–4; total 0–40) with commonly used cut-offs ≥ 8 for hazardous use and ≥ 20 for probable dependence. The DUDIT has 11 items (item scores 0–4; total 0–44) with cut-offs for hazardous use of ≥ 6 for men and ≥ 2 for women, and ≥ 25 for probable dependence. Both continuous totals and categorical classifications (none/hazardous/probable dependence) will be analyzed at T1, T2, T3, and T4 (recall periods per instrument guidance). Psychological need satisfaction and frustration will be assessed with the Basic Psychological Needs Satisfaction and Frustration Scale – Intellectual Disabilities (BPNSFS-ID; 24 items, 5-point Likert), yielding mean scores (range 1–5) for autonomy, competence, and relatedness (higher satisfaction = greater fulfillment; higher frustration = greater need thwarting) at T1, T2, T3, and T4 [35].

In addition, treatment engagement will be captured as initiation of formal SUD treatment (yes/no)—defined as attending ≥ 1 treatment session or completing an intake—within the T3 window (± 1 month post-T2); follow-through on referrals (yes/no) will be recorded separately. Participant-reported acceptability will be assessed at T2 using brief Likert-type items (e.g., clarity, relevance, burden, usefulness, overall satisfaction; 1–5) and open-ended feedback. Safety will be monitored by systematic recording of intervention-related adverse events (AEs) and serious adverse events (SAEs) at T2, T3, and T4 via structured checklists and open queries; definitions, ascertainment procedures, and reporting timelines are detailed in Harms {23}.

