### Procedure for unblinding if needed {17b}

As this study is open-label and only the data analysts are blinded, no unblinding procedures will be required.

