Treatment engagement, defined as whether a participant has initiated a formal treatment program following the intervention, will be recorded as a binary outcome (yes/no). This will be assessed at post-intervention follow-up, using a combination of self-report and verification through the referring care provider or treatment records. This outcome will serve as a behavioral indicator of the participant’s motivation to engage with care and will support the interpretation of the intervention’s practical impact. Pre-treatment assessments will also document the number of prior treatments participants have undergone. This variable will be analyzed to determine its impact on participants’ readiness and responsiveness to the intervention. Understanding participants’ treatment history will provide insights into how prior experiences influence the effectiveness of Beat the Kick and may help identify subgroups that benefit more from specific strategies.

All assessors will undergo rigorous training to ensure consistent administration of these questionnaires, led by the primary researcher. Data collection forms and instruments will be securely stored on a protected online platform accessible only to the research team.

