### Data management {19}

Data entry, coding, security, and storage will adhere to strict protocols to ensure confidentiality and accuracy. Each participant will be assigned a unique three-digit key code (001–200), linked to personal information via a list accessible only to two designated researchers. This list will be destroyed at the study’s conclusion to safeguard privacy. Sensitive data will be stored on secure servers at Tilburg University, with anonymized datasets archived in Dataverse, the university’s centralized research data repository.

To ensure pseudonymization during data collection, participants will be assigned a unique code before completing questionnaires. Participants will only enter this code on their questionnaires, avoiding any personal identifiers. If researchers assist in completing the questionnaires, they will not record identifying details, linking responses solely to the assigned code. Digital surveys will be configured to prevent the collection of IP addresses or other metadata that could compromise pseudonymization. A separate logbook will securely store the key linking participant names to codes, which will be permanently deleted upon study completion. Researchers involved in data collection will receive training from the study coordinator to ensure compliance with these anonymization protocols. All pseudonymized data will be stored on secure servers at Tilburg University for a period of 15 years, in line with Dutch regulations, after which they will be destroyed.

A comprehensive logbook will document all data collection activities, including measurements, dates, and participant details. The data management plan will follow FAIR principles (Findable, Accessible, Interoperable, Reusable), ensuring future usability while adhering to international privacy regulations overseen by institutional privacy officers. Findings will be disseminated through open-access publications and relevant platforms.

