### Adverse event reporting and harms {22}

Adverse events will be closely monitored throughout the study. Harms are defined as any adverse psychological, behavioral, or medical event related to participation, including (but not limited to) increased distress, relapse episodes, psychiatric crisis requiring intervention, or hospitalization.

All reported or observed adverse events will be documented in detail (event, onset/offset, severity, relatedness, expectedness, action taken, outcome), including an assessment of severity and potential relationship to the intervention by the primary researcher. Ascertainment will occur during each study contact (T2, T3, T4) via participant self-report and facilitator observation, with additional spontaneous reporting allowed at any time; relevant chart information will be reviewed where applicable. SAEs will be reported to the Ethics Review Board within 24 h. If necessary, protocol modifications will be implemented promptly to ensure participant safety.

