Importantly, the focus on pre-treatment motivation reflects growing recognition that many individuals with MID and substance abuse issues fall into a treatment gap—not yet motivated or eligible for intensive addiction treatment, yet clearly in need of support [8, 27]. Previous research on the earlier version of Beat the Kick showed promising outcomes using a single-case experimental design [21], but generalizability remained limited. The current RCT responds to this limitation by testing the intervention across six care organizations, enhancing external validity.

Nonetheless, several limitations must be considered. Due to the nature of the intervention, neither participants nor facilitators could be blinded to group assignment, which increases the risk of performance bias [37]. Additionally, reliance on self-report measures for substance use and psychological needs may introduce social desirability bias—particularly relevant in MID populations, who are known to provide socially desirable answers [13]. However, the instruments used in this study have been validated in this population and were supported with visual aids to facilitate comprehension and reduce misunderstanding [23, 35, 39].

Another important consideration concerns participant dropout, which is a known challenge in studies involving individuals with co-occurring MID and substance abuse problems [1, 10, 28]. Despite proactive strategies to support retention—such as flexible scheduling and involvement of caregivers—a certain level of dropout is expected. Beyond its quantitative impact on statistical power, dropout may also introduce systematic bias, particularly if individuals who discontinue differ meaningfully from those who remain in the study. For instance, participants with lower verbal ability, greater psychological distress, or more unstable living conditions may be more likely to disengage, thereby skewing the sample towards individuals with more stable or supportive environments.

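### The protocol gives two incompatible ways of collecting the TSRQ and masks only the analyst, so help at T2 could differ by arm and bias the primary endpoint

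*Protocol article*

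**What the plan says.** On how questionnaires are completed, the protocol article says three things:

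- Outcomes {12}: "To optimize comprehension for MID/BIF participants, all self-reports will be interviewer-assisted".
- Who will obtain informed consent {26a}: "All questionnaires will be completed digitally or on paper, with assistance from the researcher if needed".
- Data management {19}: "If researchers assist in completing the questionnaires, they will not record identifying details, linking responses solely to the assigned code".

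Table 2 lists the TSRQ as a questionnaire answered by the participant at T1 to T4, so all three statements apply to it. Outcomes {12} defines the primary endpoint as the change from T1 to T2 on its autonomous motivation subscale.

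On blinding, item {17b} opens: "As this study is open-label and only the data analysts are blinded". The abstract likewise limits blinding to the statistical analyst, through A/B-coded data. The abstract and {26a} have Tilburg researchers obtain consent after allocation, with different content for each arm. In {26a}, CAU participants are told their allocation.

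The safeguard stated for assessors is in {18a}: "All assessors will undergo rigorous training to ensure consistent administration of these questionnaires, led by the primary researcher". The abstract's answer to open-label bias is exclusive trainers per arm, supportive scheduling and caregiver involvement. The Discussion concedes that participants and facilitators are unblinded. It raises social desirability for substance use and psychological needs, calling it "particularly relevant in MID populations, who are known to provide socially desirable answers". It does not apply that limitation to the TSRQ, and it does not mention assessors.

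**The concern.** The TSRQ is subjective, and its items ask about the very construct that Beat the Kick sets out to change. If a researcher helps with the answers, the wording of a prompt or the decision to help at all can move the score. This is harmless to the comparison while help is the same in both arms. Under the conditional rule, help is a matter of judgement, and the plan does not keep the person judging from knowing the arm.

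The protocol itself says that this population tends towards socially desirable answers, which supplies a mechanism. Coding the dataset A/B acts only after the scores exist. Trainer separation acts on delivery, not on the interview. Any arm-related shift at T2 would enter the estimated effect directly, and no later analysis could reliably separate it from a real one.

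**Working it through.** **1. The two modes.** Under {12}, every participant is assisted. Under {26a} and {19}, some are and some are not. A site following one rule breaks the other whenever a participant would complete the form unaided.

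**2. When this can bias the comparison.** A mode effect cancels if the share assisted, and the way of assisting, are equal across arms at each wave. It biases the T1-to-T2 contrast only if they differ by arm at T2 in a way not matched at T1. Under {12}, the share assisted cannot differ, though prompting still can. Under {26a}, both can.

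**3. Knowledge of the arm.** At T2, allocation has been made, consent has been arm-specific, and blinding is confined to the analyst. At T1 it is unclear: {16b} and {16c} place assignment after baseline assessment, while the abstract and {26a} place consent after allocation.

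**4. The plan's own figures.** Inputs from Sample size {14}: f = 0.25, two groups, m = 4 measurements, correlation 0.5, ε = 1, two-sided 5%, 80% power.

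- Noncentrality λ = f² × N × m / (1 + (m − 1)ρ). For N = 82: 0.0625 × 82 × 4 / 2.5 = 8.2, power 0.808. For N = 80: λ = 8.0, power 0.798. So 82 is the smallest even N reaching 80%.
- Dropout: 82 / (1 − 0.40) = 136.7, hence 137, or 138 for equal arms.

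Both stated figures reproduce, and this point does not affect them. For two equal groups d = 2f = 0.5 SD.

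**5. Illustration of size.** The documents give no figure for interview bias. Assume no true effect and an arm-related shift b at T2, in SD of the raw score. With correlation 0.5, the SD of the change is √(2(1 − 0.5)) = 1. The baseline-adjusted residual SD is √(1 − 0.25) = 0.866. Noncentrality = b / (SD × √(2/n)), with a two-sided 5% t-test on 2n − 2 degrees of freedom.

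| n per arm | b | Rejection, change score | Rejection, baseline-adjusted |
|---|---|---|---|
| 41 | 0 | 5.0% | 5.0% |
| 41 | 0.1 | 7.3% | 8.1% |
| 41 | 0.2 | 14.6% | 17.8% |
| 69 | 0.1 | 9.0% | 10.3% |
| 69 | 0.2 | 21.5% | 27.0% |

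Here 41 is half of 82, and 69 is the full randomised arm. Against d = 0.5, shifts of 0.1 and 0.2 SD are 20% and 40% of the planned effect. Retaining more participants raises the false-positive rate, because the bias does not shrink with n.

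**The case against.** A fair defence has several parts.

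- **The modes may be partly compatible.** An interviewer could be present for everyone, on digital or paper forms, helping as required. That is a possible practice, but neither section says so, and {19} again treats assistance as something that may not happen. The wording needs reconciling.
- **A reader might infer that the T2 interviewer knows the arm, or is the person who took consent.** The documents do not say this. {18a} speaks of assessors, {26a} of the researcher, and {16c} gives consent to the primary researcher; none names who conducts the T2 interviews. What stands is that nothing in the plan prevents that knowledge.
- **A reader might infer that facilitators sit in on the TSRQ.** Item {22} refers to information gathered "via participant self-report and facilitator observation", but that concerns adverse events only and is no evidence about the primary outcome.
- **Much of the bias would survive.** Participants know their arm and the outcome is self-report. Their own tendency to please after ten sessions remains with a masked interviewer. This is correct, and it limits what the fix can achieve.
- **Assessors are trained for consistency.** This helps, but training to a protocol that gives two modes does not settle which one is used, and training does not mask.
- **Operational detail belongs in a manual.** True of rosters and forms, so their absence is no fault. The conflict over mode and the explicit restriction of blinding to the analyst are stated in the article itself.

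**Conclusion.** The point holds in this form: the mode of collecting the primary outcome is contradictory, and the plan leaves open that whoever assists at T2 knows the arm. Help or prompting could then differ by arm and bias the primary endpoint. This detection bias on the TSRQ is neither addressed nor acknowledged.

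Three stronger conclusions are tempting and are not supported. The conflict in wording does not by itself create a group difference; that requires help to differ by arm. The direction is not established: a shift towards Beat the Kick is plausible, but no passage shows it. The error rate is not known to be inflated: the 7–18% with 41 per arm follows wholly from the assumed 0.1–0.2 SD, a zero true effect and correlation 0.5.

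The change is worth making before T2 data are collected, because analysis cannot repair it afterwards. The sample size stands.

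**What to change.** - Reconcile {12}, {26a} and {19} to one mode: every TSRQ item read aloud from a fixed script with the same visual aids, in both arms and at every wave. No trainer, helper or support staff member assists.
- At T2, administer the TSRQ before the acceptability and adverse-event questions, since those can reveal the arm.
- Within the existing trained assessor team, assign T2–T4 interviews where possible to people who did not take that participant's consent and who neither deliver nor review sessions. Do not give them the arm.
- Record the assessor and the suspected arm for a sensitivity analysis.
- Amend the abstract and {17b} to match. Add to the limitations in the Discussion that detection and social-desirability bias also apply to the TSRQ.

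The single script and the order of questions cost little beyond wording. Assessor separation constrains scheduling somewhat. The documents do not give the size of the team, so it cannot be assumed that full separation needs no extra staff; hence the qualification. Masking will be partial because some participants will reveal their arm, and participants' own open-label response bias remains.
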